#### Secondary Objectives

• To describe the profile of detectable autoantibodies over a 48-weeks follow-up in patients with cancer treated with ICIs, regardless of whether they develop irAEs• To compare irAE-free survival among patients positive for autoantibodies before ICI initiation, patients positive for autoantibodies after ICI initiation and patients negative for autoantibodies throughout follow-up• To analyze cancer-related survival in patients treated with ICIs who develop irAEs and compare it with that in patients who do not develop irAEs• To investigate the potential early appearance and/or aggregation of autoantibodies over time up to the time of irAEs diagnosis.

This study protocol corresponds to the first phase of the AUTENTIC project, which will be followed by an external validation of a predictive model of irAEs with prospective data in an independent cohort of patients.

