### Follow-Up Methods

Once enrolled in the study, patients will be monitored following standard recommendations. In accordance with clinical practice guidelines (Schneider et al., 2021; Schneider et al., 2022), all patients will be assessed in a treatment planning visit at baseline. In this initial visit, attending physicians will take a detailed personal and family history focused on ADs, chronic infectious and organ-specific diseases, and conduct a physical examination. In addition, to guide their care, patients will undergo a baseline blood test including a complete blood count, measurement of glucose and thyroid stimulating hormone (TSH) levels and lipid profile, renal and liver function tests, coagulation tests, and serological tests for hepatitis B and C viruses and HIV.

The frequency of follow-up will depend on the treatment schedule of each specific ICI, discretion of the attending physician and occurrence of complications (irAEs, non-immune-related toxicity, infections). All patients will have direct telephone access to the investigators in order to report early symptoms potentially related to the occurrence of irAEs*.* Treatment schedules of the ICIs will be classified into every 2 or 3 weeks up to week 12; thereafter, drug administration may be spaced out to every 4 or every 6 weeks, respectively, according to the drug data sheets.

Two types of blood samples will be taken for research purposes only: ordinary samples, defined as those drawn routinely as scheduled (Figure 1 and Figure 2), and extraordinary samples, defined as those taken at the time an irAE is detected. As far as possible, ordinary blood samples will be collected at the same time as blood draws for medical purposes before the administration of each ICI dose, in accordance with the study schedules (Figures 1, 2).

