#### Ordinary Samples and Study Schedules

Prior to receiving the first dose of ICI, all patients will undergo a baseline (i.e., week 0) blood test for research purposes, at the same time as their baseline blood test for medical purposes.

For ICIs administered every 2 weeks (nivolumab, avelumab, and durvalumab), sequential blood tests will be performed per protocol at weeks 2, 6, 12, 24, 36 and 48 after ICI initiation, all of them at the same time as draws for medical purposes (Figure 1). In other words, four ordinary samples will be obtained in the first 12 weeks (i.e., at 0, 2, 6, and 12 weeks after ICI initiation). Thereafter, the ordinary blood sampling interval will be every 12 weeks up to the end of follow-up at week 48.

For ICIs or combinations of ICIs administered every 3 weeks (ipilimumab plus nivolumab, pembrolizumab, and atezolizumab), sequential blood tests will be performed at weeks 0, 3, 6, 12, 24, 36 and 48 after ICI initiation, all of them at the same time as draws for medical purposes (Figure 2). In other words, four ordinary samples will be obtained in the first 12 weeks (i.e., at 0, 3, 6, 12 weeks after ICI initiation). Thereafter, the ordinary blood sampling interval will be 12 weeks up to the end of follow-up at week 48.

In the event of a delay in the administration of an ICI dose due to any eventuality other than an irAE, the ordinary sample corresponding to that treatment cycle will not be obtained. If the delay is due to the occurrence of an irAE, then an extraordinary sample will be obtained, as per protocol (see “*Extraordinary samples*” in the next section). Once treatment resumes, the ordinary sample corresponding to that treatment cycle will be collected per protocol.

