### Sample Size Calculation and Statistical Analysis

To estimate an expected sensitivity of the autoantibody panel under study of 0.90 with a 95% confidence interval of not less than 0.75, 70 cases with irAEs will be needed. Considering irAEs associated with ICIs will develop in 25% of cases (Wang et al., 2019), a total of 210 patients without irAEs will be required. Considering a loss to follow-up of 5%, we should recruit a total of 294 patients.

Regarding the statistical analysis, firstly, a description of the cohort will be performed. Quantitative variables will be reported as mean ± standard deviation or median (interquartile range) and compared between groups using Student’s t-test for unpaired data or the Mann-Whitney U-test, depending on whether data follow a normal distribution. Categorical variables will be expressed as frequencies (percentages) and compared between groups using Pearson’s Χ^2^ or Fisher’s exact test based on the expected frequency of cells. To assess the primary endpoint of the study (i.e., proportion of patients developing at least an irAE), the autoantibody panel will be considered positive when any of the autoantibodies included in the panel is positive according to the following cut-off points: ANA titers ≥ 1:40, ANCA titers ≥ 1:20 or RF value ≥ 30 IU/ml. The autoantibody panel and the titers of autoantibodies will be handled as a categorical variable (namely, positive or negative result) and as a quantitative variable, respectively. It is planned to perform a subgroup analysis depending on whether or not patients have an AD before their inclusion. An analysis of variance for repeated measures will be performed to explore the profile of detectable autoantibodies over the 48 weeks of follow-up.

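### The repeated-measures ANOVA for the 48-week autoantibody profile keeps only patients with every sample, so it describes mainly survivors with complete sampling, and it suits positive/negative and titre data poorly

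*Protocol article*

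**What the plan says.** The statistical section of the protocol article names one method for the longitudinal antibody data: "An analysis of variance for repeated measures will be performed to explore the profile of detectable autoantibodies over the 48 weeks of follow-up". No mixed model, estimating-equation method or imputation is named beside it. The same section treats the panel as a positive/negative variable and the titres as quantitative.

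The objective served is the first one listed under Secondary Objectives, and it reads: "To describe the profile of detectable autoantibodies over a 48-weeks follow-up in patients with cancer treated with ICIs, regardless of whether they develop irAEs".

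Ordinary Samples and Study Schedules sets the sampling times. After a baseline sample, patients on two-weekly drugs have this plan: "sequential blood tests will be performed per protocol at weeks 2, 6, 12, 24, 36 and 48 after ICI initiation". For three-weekly drugs: "sequential blood tests will be performed at weeks 0, 3, 6, 12, 24, 36 and 48 after ICI initiation". Each patient therefore has seven planned ordinary samples.

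That section also governs delays. If a dose is delayed for a reason other than an irAE, "the ordinary sample corresponding to that treatment cycle will not be obtained". For irAE delays: "If the delay is due to the occurrence of an irAE, then an extraordinary sample will be obtained, as per protocol". The paragraph ends: "Once treatment resumes, the ordinary sample corresponding to that treatment cycle will be collected per protocol". Follow-Up Methods links the draws to dosing, as far as possible: "before the administration of each ICI dose, in accordance with the study schedules".

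**The concern.** Classical repeated-measures ANOVA needs a value at every level of the within-patient factor. One missing value out of seven removes the patient's other six. This matters because gaps are foreseeable and probably not random. Some arise by rule, after non-irAE delays. Others arise from death: tumours of any stage are eligible and only a life expectancy under 3 months is excluded (Participants), against 48 weeks of follow-up. The only stated handling of loss is censoring (Setting and Duration), which serves the survival analyses but does nothing for an ANOVA.

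At stake is a profile that leans towards patients who live to week 48 and miss no draw, reported under an objective about all treated patients. The Discussion gives the lack of prospective data on antibody status over time as a gap in existing research, so the serial samples are one of the study's main assets.

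A second problem would remain with no missing data. The outcome is either binary or a serial-dilution titre with nothing measured below the first dilution. A normal-error model with a common covariance pattern describes neither well.

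**Working it through.** **The plan's own figure.** 70 cases / 0.25 = 280 patients, of whom 210 are non-cases; 280 × 1.05 = 294. (Dividing instead, 280 / 0.95 = 294.7, gives 295.) The 294 reproduces. It was set for the sensitivity of the panel and not for this ANOVA, which has no planning figure.

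**Common time points.** Two-weekly: 0, 2, 6, 12, 24, 36, 48. Three-weekly: 0, 3, 6, 12, 24, 36, 48. Shared: 0, 6, 12, 24, 36, 48, which is six of seven. Only the second draw differs, by one week.

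**Complete cases.** Let *s* be the share with no week-48 sample and *m* the chance that any one of the six post-baseline samples is otherwise missed, with misses independent. The share complete is (1 − *s*)(1 − *m*)^6. The article gives neither input for this purpose. Its 5% loss to follow-up is the nearest figure, and it need not include deaths. All rows are therefore illustrations.

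| *s* | *m* | Share complete | Patients of 294 |
|---|---|---|---|
| 0.05 | 0.05 | 0.95 × 0.735 = 0.698 | 205 |
| 0.30 | 0.03 | 0.70 × 0.833 = 0.583 | 171 |
| 0.30 | 0.05 | 0.70 × 0.735 = 0.515 | 151 |
| 0.50 | 0.05 | 0.50 × 0.735 = 0.368 | 108 |
| 0.50 | 0.10 | 0.50 × 0.531 = 0.266 | 78 |

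Leaving out the week 2/3 draw changes little. In the first row, 0.95 × 0.95^5 = 0.735, or 216 patients instead of 205. A wider grid (*s* from 5% to 60%, *m* from 0 to 10%) runs from 279 down to 62.

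**Direction of the error.** In a simulation with assumed parameters, 294 patients had seven visits, a true mean rise of 0.90, dropout more likely after a high previous value, and 5% sporadic misses. On average 73% of samples were present but only 39% of patients were complete. The complete patients showed a rise of 0.76 and a baseline mean 0.42 SD too low; a mixed model on all samples gave 0.88. The simulated outcome was normal and dropout depended only on observed values, which favours the mixed model. The run shows the mechanism and does not forecast this cohort.

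**Type of outcome.** Data Sources and Measurements has ANA read by serial dilution and positive from 1:40 on rodent tissue or 1:80 on HEp-2 cells, and ANCA positive from 1:20. Results below the first dilution have no titre. In the pilot study described in the Discussion, 30% of patients without irAEs were panel positive, so 70% were negative. If this cohort is similar, many values will sit at the floor.

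**The case against.** The strongest defence is that this is one sentence about exploring one secondary, descriptive objective. Missing-data handling and covariance structure are details that an article commonly leaves to a fuller document. The scope argument stands: the primary objectives and the 294 do not depend on it. The omission argument does not meet the point, because the method is named, and its restriction to complete patients comes with it in the classical form.

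A reader might also infer more than the article supports:

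- *That the schedules have no common time points.* Six of seven coincide, and the week 2 or 3 draw can be treated as one visit or left out.
- *That any interruption removes a patient.* A delay matters only if it falls on a sampling visit. After an irAE delay the ordinary sample is still collected once treatment resumes, late against its nominal week. The closing sentence on resumption might even be read as covering both kinds of delay, though that sits badly with the plain statement that the sample after a non-irAE delay is not obtained. Foreseeable deaths remain on either reading.
- *That patients withdrawn for irAEs drop out of the profile.* The article does not say whether ordinary sampling continues after permanent withdrawal. Follow-up runs to week 48 from inclusion, and the full protocol may settle it.
- *That the samples of incomplete patients go unused.* They are lost to this ANOVA only. Time to autoantibody appearance and the comparison of irAE-free survival by antibody status can still use them.

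Finally, replacing the method is not a complete cure. Unweighted GEE needs data missing completely at random. A mixed model needs data missing at random and implicitly extends trajectories past death.

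**Conclusion.** The concern holds for this one secondary analysis. The method named keeps only patients with all scheduled samples, while the sampling rule for non-irAE delays and foreseeable deaths make gaps likely. The profile would therefore describe mainly survivors with complete sampling, and not all treated patients as the objective intends. The poor fit to binary results and floor-limited titres is a separate weakness and needs no assumption about attrition.

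The amount lost cannot be derived from the article. Even the mild case, an assumed 5% without a week-48 sample and 5% missed per visit, removes about 30% of patients (205 of 294 kept). The heavier assumptions keep 78 to 171. These counts rest on assumed rates and independent misses, and should be quoted only as illustrations. The change is worth making because it is cheap and protects the serial data; the study's main conclusions do not hinge on it.

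**What to change.** Replace the ANOVA sentence with:

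- a mixed logistic model for positivity of each antibody and of the panel;
- a linear mixed model for log RF and for log2 titre, with an ordinal or censored version where many titres lie below the first dilution;
- actual sampling week as the time variable, and all available ordinary samples included.

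State that the profile is that of patients alive at each time. Add a sensitivity analysis for dropout related to death or stopping of treatment. If GEE is preferred, weight it for dropout. State also whether ordinary samples continue after permanent withdrawal, since this decides whose data the models can use.

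The cost is a few sentences of analysis text and slightly more analysis work; a censored titre model may need software beyond the package named. No new data or change in sample size is required.

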### Endpoints

The primary endpoint of the study will be the proportion of patients developing at least an irAE at week 48 after the initiation of ICI therapy. An irAE was defined as any symptom, sign, syndrome, or disease caused by an immune-activating mechanism during the administration of an ICI once other causes such as an infectious disease or tumor progression have been ruled out.

Key secondary endpoints will be irAE-free survival, progression-free survival, cancer-related survival and overall survival. Other secondary outcomes will be proportion of ICI withdrawal due to the occurrence of irAEs, time to autoantibody appearance and number of positive autoantibodies included in the panel at week 48 after the initiation of ICI therapy.

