### Setting and Duration

The current study will consecutively enroll patients diagnosed with different types and stages of solid organ malignant tumors who are candidates for treatment with ICIs. In the setting of outpatient clinics, patients will be recruited by the medical oncologists responsible for their care in one of the participating hospitals. Recruitment will continue until the desired sample size is reached (see “*Study size calculation*” section). The autoantibody panel under study will be performed when the whole cohort reaches week 48 of follow-up from the time of inclusion, which will coincide with the ICI initiation date. Patients lost to follow-up will be censored at the time of their last follow-up.

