### Participants

All patients diagnosed with a solid organ malignant tumour of any stage amenable to ICI therapy according to current guidelines are potentially eligible to participate. Patients will be included by the medical oncologists in charge in the outpatient clinic setting.

The patients must meet all the following inclusion criteria:1) Initiation of treatment with an ICI or a combination of ICIs2) ICI naïve status, though those treated in the past with other systemic therapies for cancer, such as chemotherapy or tyrosine-kinase inhibitors, may be included3) Provision of written informed consent.

Exclusion criteria will be the following:1) Life expectancy of less than 3 months from the start of ICI therapy2) Contraindication to ICI therapy: proven hypersensitivity or history of anaphylactic allergic reactions secondary to ICIs, active severe autoimmune disease, or poor performance status (Eastern Cooperative Oncology Group score ≥ 3)3) Active immunosuppressive treatment: prednisone at doses >10 mg/day or equivalent (e.g., 1.5 mg/day of dexamethasone), azathioprine, methotrexate, mycophenolate, cyclophosphamide, rituximab, leflunomide, anti-tumor necrosis factor agents (infliximab, etanercept, adalimumab, golimumab), or abatacept, among others.

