Data related to the tumour:• Tumour type• Date of diagnosis• PD-L1 expression in tumour cells (%)• Date of initiation of ICI therapy• Dates of ICI administration• Date of progression• Date of death• Progression-free survival, defined as time from start of ICI therapy to tumor progression, death or last day of follow-up• Overall survival, defined as time from start of ICI therapy to death or the last day of follow-up• Cause of death: cancer-related, non-cancer-related, ICI-associated toxicity (immune-related, non-immune-related adverse event, infection or other).

Data related to treatment received before ICI initiation:• Nonsteroidal anti-inflammatory drugs• Glucocorticoids• Other immunomodulatory drugs: e.g., colchicine, hydroxychloroquine, mesalazine, or sulfasalazine• Oral anticoagulants (acenocoumarol, low-molecular-weight heparin, direct oral anticoagulants).

Data related to ICI:• Type: anti-CTLA4 (ipilimumab), anti-PD1 (nivolumab and pembrolizumab), anti-PD-L1 (atezolizumab, avelumab, and durvalumab)• Monotherapy or combination therapy (description)• Adjuvant or palliative therapy, and if palliative, line of therapy (first line, second line, other).

Laboratory data:

Obtained from blood samples for care and research purposes:• Glomerular filtration rate (ml/min/m^2^), levels of glucose (mg/dl), bilirubin (mg/dl), alanine aminotransferase, aspartate aminotransferase, gamma-glutamyltransferase (U/L), and thyroid stimulating hormone (μUI/mL).• Prothrombin time (percentage) or international normalized ratio (INR)• Complete cell count: haemoglobin (g/dl), white blood cells (/µL), differential white blood cell count of neutrophils, lymphocytes, monocytes, and eosinophils (/μL) and platelets (/μL)• Lipid profile: levels of cholesterol, triglycerides, and high- and low-density lipoprotein cholesterol (mg/dl).

Obtained from blood samples only for research purposes:• 25-hydroxycholecalciferol (ng/ml) at weeks 0, 24 and 48.• Levels of the autoantibodies under study (i.e., ANAs, RF and ANCAs) in ordinary samples according to study schedules (Figures 1, 2) and extraordinary samples.

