Survival will be assessed using a Kaplan-Meier analysis and compared between groups using the log-rank Mantel-Cox test. A subgroup analysis according to tumour type and extent of cancer (local, advanced, and metastatic disease) will be performed to assess survival outcomes*.* A multivariate analysis using logistic regression and Cox regression will be performed to detect factors associated with the occurrence of irAEs. Applying a manual backward stepwise procedure, a multivariate model will be constructed from variables that either have a p-value of less than 0.10 in the univariate analysis or are considered relevant to the dependent variable on the basis of previous studies (e.g., sex and age of patients, type of ICI). Variables not reaching statistical significance will be dropped from the final predictive model. The sensitivity, specificity, positive predictive value, negative predictive value, and probability ratios with their corresponding 95% confidence intervals of the model will be calculated. The diagnostic accuracy of the predictive model inferred from the logistic regression model will be described with the area under the receiver operating characteristic curve.

Two-sided hypothesis tests will be performed, and the significance level will be set at 5%. The statistical analysis will be conducted using IBM SPSS Statistics software version 27.0 (Chicago, IL).

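### irAE-free survival is analysed by Kaplan-Meier and log-rank with no stated role for death before an irAE, so its curves cannot be read as 48-week irAE risk

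*Protocol article*

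**What the plan says.** Under Endpoints, the protocol article lists this outcome first among its key secondary endpoints: "Key secondary endpoints will be irAE-free survival, progression-free survival, cancer-related survival and overall survival". The second secondary objective is "To compare irAE-free survival among patients positive for autoantibodies before ICI initiation, patients positive for autoantibodies after ICI initiation", with a third group that stays negative throughout follow-up.

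The method is in Sample Size Calculation and Statistical Analysis: "Survival will be assessed using a Kaplan-Meier analysis and compared between groups using the log-rank Mantel-Cox test". The same section plans logistic and Cox regression for factors associated with irAEs.

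The only censoring rule is in Setting and Duration: "Patients lost to follow-up will be censored at the time of their last follow-up". The section Variables defines two of the survival outcomes and names death in both: "Progression-free survival, defined as time from start of ICI therapy to tumor progression, death or last day of follow-up" and "Overall survival, defined as time from start of ICI therapy to death or the last day of follow-up". It has no matching definition for irAE-free survival. Dates of irAE diagnosis and of death, and the cause of death, are all collected.

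**The concern.** A patient who dies before any irAE can no longer have one, so death is a competing event for time to first irAE. Deaths within 48 weeks are to be expected. Tumours of any stage are eligible, survival is to be analysed by extent of cancer including metastatic disease, and the exclusion on prognosis reaches only to "Life expectancy of less than 3 months from the start of ICI therapy".

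The stated method can be run in two ways, and they answer different questions:

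- **Deaths censored.** The log-rank test compares irAE hazards among patients still alive and irAE-free. The curve, read as 1 minus Kaplan-Meier, describes irAE risk if nobody died first, which is higher than the proportion of patients who actually have an irAE.
- **Deaths as events.** The curve correctly describes survival free of both irAE and death, but a difference between antibody groups may come from mortality and not from irAEs.

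At stake is the meaning of the antibody-group comparison, and any absolute irAE risk read off the curves for each group.

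**Working it through.** **The plan's own figures.** The sample size does not depend on this point. 70 irAE cases at 25% give 70 / 0.25 = 280 patients, and 280 × 1.05 = 294, as stated. The 70 cases also reproduce as the smallest number for which the exact one-sided 95% lower limit is at least 0.75 with 95% probability when the true sensitivity is 0.90.

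**Inputs.**
- True 48-week irAE incidence, F1 = 25%: the planning figure in the sample size section.
- Death without a prior irAE by week 48, F2: not in the article, so assumed at 5 to 40%.

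**Deaths censored.** Under constant cause-specific hazards the total cumulative hazard is −ln(1 − F1 − F2), and the irAE share of it is F1 / (F1 + F2). Hence

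1 − KM = 1 − (1 − F1 − F2)^(F1 / (F1 + F2)).

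At F2 = 20%: 1 − 0.55^(0.25 / 0.45) = 1 − 0.717 = 28.3%, against a true 25%.

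**Deaths as events.** The failure proportion is F1 + F2, and the share of events that are deaths is F2 / (F1 + F2). At F2 = 20% this is 0.20 / 0.45 = 44%.

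| Death first (assumed) | 1 − KM, deaths censored | Excess over 25% (points) | Composite failure | Deaths among composite events |
|---|---|---|---|---|
| 5% | 25.7% | 0.7 | 30% | 17% |
| 10% | 26.5% | 1.5 | 35% | 29% |
| 20% | 28.3% | 3.3 | 45% | 44% |
| 30% | 30.4% | 5.4 | 55% | 55% |
| 40% | 33.2% | 8.2 | 65% | 62% |

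**Sensitivity to timing.** If irAEs come early (Weibull shape 0.6 for the irAE hazard, constant death hazard), the excess is smaller: 1.1, 2.4 and 4.0 points at 10, 20 and 30% deaths.

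**Sensitivity to incidence.** With the pilot study's 37.5% in place of 25%, the excess is 1.1 points at 5% deaths, 5.3 at 20% and 13.9 at 40%.

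**Scale.** The standard error of a 25% proportion in 280 patients is √(0.25 × 0.75 / 280) = 2.6 points, so the constant-hazard excess at 20% deaths is 3.3 / 2.6 ≈ 1.3 standard errors. In a group of about 93 (an equal three-way split, assumed) the standard error is √(0.25 × 0.75 / 93) = 4.5 points, and the same excess is about 0.7 standard errors.

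**The case against.** The strongest reply is that event and censoring rules for a secondary endpoint are often left to an analysis plan, and that neither way of running the stated method is invalid. Much of this stands:

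- With deaths censored, log-rank is a valid test of the cause-specific irAE hazard. The Cox regression already planned for irAEs is then the model recommended below.
- Survival free of irAE or death is the ordinary meaning of the endpoint's name and parallels the progression-free survival definition. Kaplan-Meier is correct for it once it is declared.
- The article does not say that 1 minus Kaplan-Meier will be reported as irAE risk. The primary endpoint is the simple week-48 proportion.
- Mortality may be modest. Adjuvant treatment is included and ECOG 3 or worse is excluded. At 5% deaths the excess is under one point.

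A reader might infer that both ways of running the analysis give a wrong answer, or that the log-rank test is invalid. The points above show why that does not follow.

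A reader might also take the overall-survival hazard ratios in the article's Table 1 (0.28 in one study, 2.31 in another) as evidence that a composite would reverse the direction of an irAE effect. The documents do not support this. Those ratios come from other antibody panels and include deaths after an irAE, and a reversal appears only when the 0.28 is combined with an irAE effect from a different study and an assumed 30% death rate. They show only that mortality may differ by antibody status.

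What does not stand is that this is merely missing detail. The article fixes the estimator and defines death's role in two sister endpoints. Kaplan-Meier cannot deliver irAE risk under either reading, so an analysis plan that reported cumulative incidence would have to depart from the stated method.

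**Conclusion.** The point holds in a limited form. The article commits irAE-free survival to Kaplan-Meier and log-rank without saying how death before an irAE counts. If deaths are censored, the test is sound but the curves overstate 48-week irAE risk. If deaths are events, the composite is sound but does not isolate irAEs.

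The size rests on an assumed death-first rate, a true incidence of 25% and constant hazards: 0.7 to 5.4 points over 5 to 30% deaths, less if irAEs come early and more if incidence is nearer the pilot's 37.5%. The change should be made, but it concerns a secondary endpoint. The primary endpoint and the 294 patients are not affected.

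**What to change.** In Endpoints and in the analysis section:

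1. Define time from ICI start to first irAE, with death without a prior irAE as a competing event.
2. Report Aalen-Johansen cumulative incidence of irAE at week 48 in place of 1 minus Kaplan-Meier.
3. Compare groups with the cause-specific Cox model for irAE, and report the hazard of death without an irAE beside it.
4. If irAE-or-death is wanted, declare it as a composite and report it in addition.
5. Draw incidence curves by baseline antibody status. Handle positivity arising after ICI start as a time-dependent covariate or by landmark. That group is defined during follow-up, so cumulative incidence curves drawn by it would still not give a valid week-48 risk.
6. Keep Kaplan-Meier and log-rank for overall and progression-free survival.

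The cost is a few sentences, slightly more analysis work and possibly software beyond the named SPSS 27. Stated irAE risks will come out slightly lower than from Kaplan-Meier with deaths censored. No extra patients, visits or data are needed. Because the antibody panel is run only once the whole cohort reaches week 48, the rule can be fixed before the panel results from the stored samples are known.

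### For cancer-related survival, PFS and OS, the irAE versus no-irAE comparison has no stated control for tumour type or extent of cancer; both enter only as subgroups

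*Protocol article*

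**What the plan says.** All references are to the protocol article.

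- **Population (Participants).** "All patients diagnosed with a solid organ malignant tumour of any stage amenable to ICI therapy" may be eligible, so adjuvant and palliative patients sit in one cohort.
- **Groups (Secondary Objectives).** One objective is "To analyze cancer-related survival in patients treated with ICIs who develop irAEs and compare it with that in patients who do not develop irAEs". The groups are formed by what happens to patients, not by randomisation. PFS, cancer-related survival and OS are among the key secondary endpoints (Endpoints).
- **Method (Sample Size Calculation and Statistical Analysis).** "Survival will be assessed using a Kaplan-Meier analysis and compared between groups using the log-rank Mantel-Cox test". On tumour: "A subgroup analysis according to tumour type and extent of cancer (local, advanced, and metastatic disease) will be performed". On modelling: "A multivariate analysis using logistic regression and Cox regression will be performed to detect factors associated with the occurrence of irAEs".
- **Confounding (Management of Confounding and Interaction Factors).** Glucocorticoid use for reasons other than an irAE is the only confounder named.
- **Variables.** Tumour type and adjuvant or palliative setting are listed among the potential predictors of irAEs.

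**The concern.** The plan treats tumour type in two ways. It lists it as a candidate predictor of irAEs, that is, of group membership in the survival comparison. It also treats it as relevant enough to survival to plan subgroups by it. A variable linked to both group and outcome is a confounder, and subgrouping does not remove its effect from the pooled test.

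If irAEs are more frequent in tumours with a better outlook, the irAE group will contain more of those patients and will appear to live longer even when irAEs have no effect on survival. The study could then report a link between toxicity and survival that is partly or wholly a difference in tumour mix.

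**Working it through.** **1. The plan's own figure.** No figure is given for any survival comparison. The stated total comes from the sensitivity calculation: 70 irAE cases / 0.25 = 280, and 280 × 1.05 = 294, as stated (280 / 0.95 gives 295). The survival checks below use 280 analysable patients, 25% with an irAE.

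**2. Which endpoints have a route to adjustment.**

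| Endpoint | Stated methods | How tumour type or extent can enter |
|---|---|---|
| irAE-free survival | Kaplan-Meier, log-rank; Cox model for irAE occurrence | Subgroups; tumour type also as a candidate covariate in the Cox model |
| Cancer-related survival | Kaplan-Meier, log-rank | Subgroups only |
| PFS, OS | Kaplan-Meier, log-rank | Subgroups only |

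**3. The mechanism by hand.** Every rate here is assumed. Take two equally common tumour types with 48-week survival 0.85 and 0.50, irAE risk 35% and 15%, and no irAE effect.
- Share with the better tumour: irAE group 0.35/(0.35+0.15) = 0.70; no-irAE group 0.65/(0.65+0.85) = 0.433.
- Expected 48-week survival: irAE 0.70×0.85 + 0.30×0.50 = 0.745; no irAE 0.433×0.85 + 0.567×0.50 = 0.652.
- Ratio of cumulative hazards: ln(0.745)/ln(0.652) ≈ 0.69, although the true ratio is 1.

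With milder differences (survival 0.80 and 0.60, irAE risk 30% and 20%) the same steps give 0.720 and 0.693, a ratio of about 0.90.

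**4. Simulation of the test.** 280 patients, exponential survival censored at week 48, two-sided 5% level, no true irAE effect, irAE status treated as known at the start. The two-type rows use 4000 runs. The four-type rows use 3000 runs, with a 50/20/15/15% mix and about 56% events. Hazard ratios (HRs) are one-step estimates from the log-rank score and its variance.

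| Assumed link between tumour and irAE | Pooled HR | Pooled false positives | Stratified HR | Stratified false positives |
|---|---|---|---|---|
| None: irAE risk 25% in all four types | 1.01 | 4.9% | 1.01 | 4.9% |
| Mild: two types, 0.80 v 0.60, irAE 30% v 20% | 0.90 | 6.0% | 1.00 | 4.5% |
| Mild: four types, irAE 20–35% | 0.88 | 10.4% | 1.01 | 4.9% |
| Moderate: four types, irAE 18–42% | 0.82 | 19.1% | 1.01 | 5.6% |
| Strong: two types, 0.85 v 0.50, irAE 35% v 15% | 0.71 | 28.7% | 1.01 | 4.8% |
| Strong: four types, irAE 17–45%, median survival 26–200 weeks | 0.72 | 45.5% | 1.01 | 5.0% |

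Repeat runs of the two-type scenarios gave 6.4–6.6% (mild) and 28.5–28.7% (strong) for the pooled test.

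**5. What subgroups can do.** Power = Φ(√(E × 0.25 × 0.75) × |ln HR| − 1.96), with E events. The event fraction is assumed at 40–70%. HRs of 0.53 and 0.66 are taken from Table 1 of the article as benchmarks of size only; they describe autoantibodies, not irAEs.

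| Share of cohort | Patients (irAE) | Events | Power, HR 0.53 | Power, HR 0.66 |
|---|---|---|---|---|
| All | 280 (70) | 112–196 | 83–97% | 48–71% |
| Half | 140 (35) | 56–98 | 54–78% | 27–43% |
| Quarter | 70 (about 18) | 28–49 | 31–49% | 16–24% |

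For example, with 49 events and HR 0.53: √(49 × 0.1875) = 3.03; 3.03 × 0.635 − 1.96 ≈ −0.04; Φ ≈ 0.49.

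**The case against.** **The text is silent on strata.** This is a condensed article, and strata for secondary endpoints are often left to an analysis plan. A reader might infer a decision to run a single unstratified test; the text does not say that. What remains is that the article does choose how tumour type and extent enter the survival analysis (as subgroups) and does say what the Cox model is for (irAE occurrence). That is a stated approach that leaves the pooled comparison uncontrolled.

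**The bias is conditional.** A reader might infer that tumour mix does distort the result. The documents give no irAE or survival rates by tumour, and with equal irAE rates the pooled test keeps its 5% level. This stands and limits the claim to a risk.

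**Cox regression is planned.** One objective is "To compare irAE-free survival among patients positive for autoantibodies before ICI initiation" and the other autoantibody groups. For that endpoint the Cox model for irAE occurrence can include tumour type, although p<0.10 screening and backward elimination may drop it. The point should not be carried over to irAE-free survival.

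**Loss of power and attenuation.** A reader might infer that pooling also pulls the HR well towards 1. With fitted Cox models and a true HR of 0.60, the pooled estimate was about 0.63 and the stratified 0.59 under an extreme split (survival 0.90 v 0.40), and 0.60 and 0.59 under 0.80 v 0.60. Power was about 36% v 48% in the extreme case and 38% v 39% in the milder one. This is not a general argument.

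**Subgroup size.** A reader might cross tumour type with extent and conclude that every cell is tiny. The article does not say that they are crossed and gives no tumour mix. A type making up half the cohort would have 54–78% power at HR 0.53. The sound objection to subgroups is that they yield several separate answers and no single comparison free of tumour mix.

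**Conclusion.** The concern holds for the irAE versus no-irAE comparison of cancer-related survival, and for PFS and OS, which fall under the same analysis sentence. The stated methods leave that comparison open to confounding by tumour type and extent. The false-positive rate depends on assumed links: about 5% with none, 6–10% with mild links, 19% with a moderate one and 29–46% with strong ones. Stratifying by tumour type kept it at 4.5–5.6% in every scenario shown. These figures rest on invented tumour mixes and rates and on irAE status known at the start, so they show direction and plausible range, not a forecast. The issue concerns key secondary endpoints. It does not affect the primary objectives, the primary endpoint or the 294 patients.

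**What to change.** In Sample Size Calculation and Statistical Analysis, state that the main irAE versus no-irAE comparison of cancer-related survival, PFS and OS will use a Cox model (or log-rank test) stratified by, or adjusted for, tumour type, with rare types merged, and extent of cancer or adjuvant/palliative setting. Report the HR from the Cox model with the same factors. Describe the tumour-type and extent subgroups as descriptive.

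The cost is a sentence or two. Tumour type and treatment setting are already listed under Variables; extent is not listed there by name, but the planned subgroup analysis needs it anyway. Merging rules for rare types should be set before the data are analysed, and sparse strata will add little information. This change does not deal with irAEs arising during follow-up rather than at the start, which needs its own handling in the same comparison.
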